### Participant follow-up

Women will be followed up over a period of approximately 26 weeks, during which two-weekly reminder texts to complete the study diary will be sent. Outcome data will be collected at the antenatal clinic appointment at 38–41 weeks of gestation (Fig. 1).

Based on the clinic attendance lists, the researcher will arrange to meet each woman at one of their antenatal appointments at 38–41 weeks of gestation as above to undertake the outcome assessment. Women will be assessed for the development of striae and the severity of striae using the assessment instruments outlined above. In addition, the following data will be collected:Gestation at assessment;Current weight (to determine weight gain [% and absolute gain] during pregnancy);BMI;Mid-abdominal circumference;Development of polyhydramnios;Gestation at onset of striae as applicable;Development of striae in other body areas;Adherence to the intervention or control guidelines or not and reasons for same;Adverse event/undesirable effect (see below);Women’s evaluation of the tolerability and the effectiveness of the intervention;Women’s perceptions of the severity of striae gravidarum.

In addition, following the birth, the researcher will collect data on the following, from the labour ward register:Gestational week at birth;Weight of infant (Fig. 1).

### Safety and undesirable effects

In keeping with the safety advice for the moisturising oil, women will be advised at recruitment that the oil is for external use only and should be kept out of the reach of children. They will be advised that in the event of a rash occurring or breathing problems or any other undesirable effect associated with the oil, that they discontinue the application of the oil and contact their general practitioner. They will also be asked to contact the researcher who will complete an undesirable effect form and the undesirable effect record log**.** The researcher will also complete a Cosmetic Product Undesirable Effect Report for the Health Products Regulatory Authority (HPRA) [38].

Adverse events for this study are classified as undesirable effects and serious undesirable effects [38] as follows:Undesirable effect – ‘…an adverse reaction to a cosmetic product under normal or foreseeable conditions of use’, (e.g. ‘…irritant and allergic effects, sensitivity to light and itching’;Serious undesirable effect – ‘…an undesirable effect which results in temporary or permanent functional incapacity, disability, hospitalization, congenital anomalies, an immediate vital risk or death’.

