### Objectives of the pilot trial

Measure recruitment, enrolment, completion, adherence and attrition (withdrawal, drop outs) rates;Evaluate recruitment and randomisation processes;Evaluate the data collection instruments;Collect qualitative data on reasons for refusal to participate; reasons for non-adherence with the intervention and control guidelines and reasons for attrition;Ascertain women’s rating of the tolerability/acceptability and effectiveness of the intervention;Measure the completeness of data collection for outcomes;Evaluate the data analysis methods.

As this is a feasibility study, formal hypothesis testing will not be performed. Suitable descriptive statistics and graphical summaries will be used to summarise participant characteristics. Means and standard deviations will be used for continuous variables; counts and percentages will be used for categorical variables with accompanying 95% CI estimates.

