#### Control intervention

Women allocated to the control group will not use any treatment and will be asked not to use any other skin product on their abdomen to maintain treatment fidelity. They will also be asked to keep a diary record (Fig. 1) and to document any product applied to their abdominal skin so that this can be assessed as part of the pilot trial.

All women will receive a two-weekly text to remind them about their participation in the trial and to complete the diary. A text message reminder will also be sent to women at 37 weeks to bring their empty oil bottles to the outcome assessment interview as appropriate.

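### Adverse events are defined only as reactions to a cosmetic product, so the adverse event item has no background rate from women who follow the control guidelines

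*Protocol article*

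**What the plan says.** The section on safety and undesirable effects sets the rule: "Adverse events for this study are classified as undesirable effects and serious undesirable effects". An undesirable effect is "an adverse reaction to a cosmetic product under normal or foreseeable conditions of use". The serious category is "an undesirable effect which results in temporary or permanent functional incapacity, disability, hospitalization, congenital anomalies, an immediate vital risk or death", so it lies inside the first and carries the same link to a product. Reporting during follow-up is prompted "in the event of a rash occurring or breathing problems or any other undesirable effect associated with the oil".

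The section on participant follow-up lists the data taken at 38–41 weeks. One item, not limited to either arm, reads "Adverse event/undesirable effect (see below" and so points to the definitions above.

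For the comparison arm the protocol states: "Women allocated to the control group will not use any treatment and will be asked not to use any other skin product on their abdomen". Control women also keep a diary and are asked "to document any product applied to their abdominal skin so that this can be assessed as part of the pilot trial".

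The objectives include women's "rating of the tolerability/acceptability and effectiveness of the intervention". This is a separate item from the adverse event record. The blinding sections state that the women, their carers, the researcher and the outcome assessor all know the allocation.

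**The concern.** The item is collected in both arms, but the definition behind it requires a product. The document's own examples, such as irritation, allergic effects and itching, are not specific to the oil. A randomised control group is the natural source of a background rate for such symptoms, and this definition gives that source up.

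What remains is a count in the oil arm that rests on a causal judgement made without blinding. The error can go either way: a complaint with another cause may be blamed on the oil, and a real effect that nobody links to the oil may be left out. A definition suited to reporting to the cosmetics regulator is doing the work of a trial definition. If pilot women are carried into the definitive trial, symptoms not asked about in pilot controls may not be recoverable later.

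**Working it through.** The plan gives no figure on this point, so the main check is to set the provisions side by side.

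1. **Scope of the definition.** There are two categories, the second nested in the first. Every adverse event of the study therefore requires attribution to a cosmetic product. The article gives no definition that covers an untoward event regardless of cause.
2. **Exposure in the control arm.** There is no treatment, and women are asked to apply no other abdominal product. For a woman who complies, no product exists to which a reaction could be attributed.
3. **The 38–41 week item.** It is listed for all women but refers to the definition in step 1. Steps 1 and 2 together give zero recordable events among control women who follow the guidelines, whatever symptoms they have.
4. **Who attributes.** The woman and the researcher do so, and both know the allocation.

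**Illustration of size.** Inputs: 20 women per arm (sample size section) and an assumed background rate b of rash or itch unrelated to the oil. Expected cases per arm are 20 × b, and the chance of at least one case among 20 is 1 − (1 − b)^20.

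| Assumed b | Expected cases of 20 | Chance of at least one |
|---|---|---|
| 5% | 1 | 64% |
| 10% | 2 | 88% |
| 20% | 4 | 99% |
| 25% | 5 | not computed |

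Suppose the oil has no effect, b is 20%, every oil-arm symptom is attributed to the oil, and all control women comply. The record would then show 4/20 against 0/20. The Newcombe interval for the difference uses the Wilson limits of each arm: 0.081 to 0.416 for 4/20, and 0 to 0.161 for 0/20.

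- Difference: 0.20 − 0 = 0.20.
- Lower limit: 0.20 − √[(0.20 − 0.081)² + (0.161 − 0)²] = 0.20 − 0.20, or −0.001 with unrounded inputs.
- Upper limit: 0.20 + √[(0.416 − 0.20)² + 0²] = 0.416.

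The apparent difference is 20 percentage points (95% CI −0.1 to 41.6). Counted alike in both arms, 4/20 against 4/20 gives 0 (−24.7 to 24.7). At b = 5%, 1/20 against 0/20 gives 5 points (−11.6 to 23.6). All these one-sided contrasts are upper bounds, because they assume complete attribution to the oil.

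The planned size of the definitive trial plays no part here. It reproduces as 91 per arm before attrition, 91 / 0.8 = 113.75, rounded up to 114, and the point does not change it.

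**The case against.** The strongest reply is that the oil is a marketed cosmetic, the definition is the cited reporting definition for such products, and a 40-woman feasibility study may reasonably adopt it. Adverse events are not in the list of outcome measures, they are not a criterion for proceeding to the main trial, no formal hypothesis testing will be done, and no safety comparison between arms is announced. All of this stands, and it is why the point is minor. It does not explain why the item is collected from women who cannot qualify for it.

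The documents do not support several stronger readings that a reader might infer:

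- *The control arm can have no event at all.* The definition refers to a cosmetic product, not to the trial oil. The protocol foresees that control women may apply something and has it recorded in the diary. A reaction to such a product would qualify. Zero by construction holds only for control women who follow the guidelines.
- *The tolerability outcome has lost its comparison.* That outcome is a rating of the intervention. Control women have no intervention to rate, so it has no control counterpart under any adverse event definition.
- *Every background complaint will be counted against the oil, or a symptom not blamed on the oil is never recorded.* Neither is established. In the reporting instruction, the link to the oil may qualify only the other effects and not rash or breathing problems. The diary and the outcome and undesirable effect forms are not shown and may ask more. The Trial Steering Committee also reviews reported trial-related effects, although only those already reported.
- *The definitive trial will inherit a biased safety comparison.* Pooling is conditional on feasibility, and the stated hypothesis of that trial concerns only the occurrence and severity of striae.

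**Conclusion.** The point holds for the adverse event item at 38–41 weeks. The only definition behind it requires attribution to a cosmetic product, so control women who comply contribute no events, and the oil arm's rash or itch count has no concurrent background rate and depends on unblinded attribution.

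The documents do not allow the size to be estimated. With an assumed background rate of 5–25%, at most 1 to 5 of 20 oil-arm women against 0 of 20 controls could appear with no true effect. The upper bound rests on that assumed rate, full attribution to the oil and full compliance in the control arm.

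No pilot decision rule and no sample size changes. The consequence for the descriptive pilot is modest, and larger if its data are carried into the definitive trial. Severity is minor, and the improvement is cheap.

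**What to change.** Keep the cosmetic-product definition for reports to the regulator. In addition:

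- Ask women in both arms the same short list of abdominal skin symptoms, regardless of cause, in the existing diary and on the 38–41 week form. The protocol's own examples (irritation, allergic effects, itching, sensitivity to light) can serve as the list.
- Record attribution to a product, and which product, as a separate field.
- Report symptom counts by arm descriptively with 95% confidence intervals, in line with the planned handling of categorical variables.

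If the forms not shown already ask such questions in both arms, only the definition and the reference to it need rewording.

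The cost is a few form lines and some additional minor complaints recorded. Both arms already keep a diary and attend the assessment, and the trial status section reports that no participant had been enrolled, so at that protocol version the change could be made before any data were lost.

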#### Outcome measures

In order to evaluate the feasibility of conducting a definitive randomised controlled trial to evaluate the effectiveness of a moisturising oil (commercially available moisturising oil) compared to no treatment for the prevention and reduction in severity of striae gravidarum, the outcomes for this pilot study are:Number and proportion of women who are recruited, enrolled, complete the study and adhere to the intervention and control guidelines;Percentage of potentially eligible women who are recruited/enrolled to the study;Challenges with the randomisation process;Number and proportion of women who withdraw, drop out or deviate from the protocol guidelines;Reasons for non-recruitment, non-adherence or attrition;Women’s rating of the tolerability/acceptability and effectiveness of the intervention;Completeness of data collection for outcomes;Challenges with data analysis;Number and proportion of women developing striae gravidarum in the intervention and control groups;Number and proportion of women developing mild, moderate or severe striae gravidarum;Women’s perception of the severity of striae gravidarum (Fig. 1).

In addition to the above outcomes, birth data will also be collected following each birth from the labour ward register on birth gestation and infant weight (Fig. 1) and recorded on the outcomes assessment form.

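### Serious effects first recognised at or after birth, and any effect in women who give birth before the 38–41 week visit, are not systematically collected

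*Protocol article*

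**What the plan says.** The protocol article, under Safety and undesirable effects, sorts adverse events into two classes. An undesirable effect is "an adverse reaction to a cosmetic product under normal or foreseeable conditions of use". A serious one is an undesirable effect with a grave result, and the listed results end with "disability, hospitalization, congenital anomalies, an immediate vital risk or death".

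Collection is set out under Participant follow-up:

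- "Women will be followed up over a period of approximately 26 weeks".
- "Outcome data will be collected at the antenatal clinic appointment at 38–41 weeks of gestation". The items gathered there include one that begins "Adverse event/undesirable effect (see below").
- After the birth the researcher takes two items "from the labour ward register:Gestational week at birth;Weight of infant".

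Outcome measures repeats the last of these: "birth data will also be collected following each birth from the labour ward register on birth gestation and infant weight".

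There is one other route. Women are told to get in touch with the researcher about a rash, breathing problems or another effect associated with the oil. The researcher then completes a form, a log and a report to the regulator. The article gives no closing date for this route. The Trial Steering Committee reviews the cases that are reported.

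**The concern.** The safety definition reaches further than the data collection. A congenital anomaly is often first recorded at birth, and a neonatal admission or neonatal death can only follow it. Yet the one scheduled safety question is asked while the woman is still pregnant, and neither of the two post-birth items describes the condition of the infant.

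A woman who gives birth before her appointment also misses the scheduled question altogether, even for ordinary effects such as a rash. The article describes no substitute contact for her.

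The stake is the completeness of the safety record. If the pilot lists no infant or birth-related effect, a reader cannot tell whether none occurred or none was sought. Evaluating the data collection instruments is a stated pilot objective. The pilot women are also meant to be carried into the definitive trial, so a field left out now could be filled for them later only by reopening records.

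**Working it through.** The plan gives no figure for safety ascertainment, so there is nothing of its own to reproduce; the sample size of 228 does not enter. The check compares definition, timing and content.

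**1. Timing.** Recruitment is at 12–16 weeks and follow-up lasts about 26 weeks: 12 + 26 = 38 and 16 + 26 = 42 weeks. Follow-up is thus built around the antenatal visit at 38–41 weeks. From entry to visit the interval is between 38 − 16 = 22 and 41 − 12 = 29 weeks, all of it before birth. Scheduled safety contacts described after birth: none.

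**2. Content after birth.** Both statements of the post-birth data give the same list: "Gestational week at birth;Weight of infant". Set against the serious results in the definition:

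| Event, if a reaction to the product | Scheduled question at 38–41 weeks | Post-birth extraction | Woman's own report |
|---|---|---|---|
| Maternal hospitalisation before the visit | can be captured | no | possible |
| Congenital anomaly diagnosed antenatally | can be captured | no | possible |
| Congenital anomaly first seen at birth | no | no | possible |
| Neonatal admission or death | no | no | possible |
| Any effect in a woman who delivers before her visit | no | no | possible |

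The last three rows depend on self-report alone. That route asks the woman to make the causal link herself, and the advice mentions neither the infant nor the birth.

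**3. Extent.** The pilot has 20 women per arm, 2 × 20 = 40 in all. The infant's condition is on the stated list for none of the 40, although the register is to be consulted after each birth. The definition concerns reactions to the oil, so it bears directly on the 20 women allocated to it.

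The article does not give the number who deliver before their visit. Two assumed shares show the range: 5% gives 0.05 × 40 = 2 women. A share of 20%, the limit that the progression criteria set for loss to follow-up, gives 0.20 × 40 = 8. The second is only a reference point, because the article does not say whether such women count as lost.

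**The case against.** The strongest reply is that the definition is a quoted one for cosmetic products. It covers reactions to the product and serves to classify and report them; it does not promise to ascertain every birth outcome. An anomaly or a neonatal admission is not in itself a serious undesirable effect, and women in the control arm use no oil. This stands. There is no outright contradiction, and collecting birth outcomes in both arms goes wider than the definition. But relatedness can be judged only for events that someone has recorded, and self-report leaves that first judgement to the woman.

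Three stronger readings are tempting and do not hold:

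- *That such effects cannot be found.* Self-report has no stated end date, and events before the visit can surface there. The text supports only a lack of systematic ascertainment.
- *That an empty safety list would be the basis for moving to 228 women.* The three progression criteria are recruitment, adherence and loss to follow-up; none concerns safety.
- *That a confidence limit measures the gap.* For 0 of 20 the exact two-sided 95% upper limit is 1 − 0.025^(1/20) = 16.8%. That reflects the size of the arm and would be the same with perfect collection.

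It can also be said that the article is condensed, and that the schedule figure, the forms and the full protocol may add procedures. That is possible. However, the post-birth data are given twice as a specific list, each time with reference to that figure, so the point rests on what is stated.

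**Conclusion.** The point holds as a modest gap in collection. As described, effects first recognised at or after birth, and every effect in a woman who delivers before her visit, rely on her contacting the researcher about something she links to the oil.

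The first part applies across all 40 planned pregnancies, with 20 in the oil arm. The second applies to an unknown number, illustrated above as 2 to 8. No planned estimate, feasibility outcome or progression criterion is altered. Even with full collection the pilot could not compare the arms on such events.

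The conclusion assumes that the two matching lists of post-birth data are complete and that no further safety contact is set out in the documents not shown. It is worth acting on because the change is small and, at the stated protocol version, nobody had been enrolled.

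**What to change.** Reconcile Safety and undesirable effects with Outcome measures and Participant follow-up:

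1. Add three items to the existing post-birth extraction, in both arms: live birth or stillbirth, congenital anomaly recorded, and neonatal admission. Use the labour ward register, or the hospital record where the register does not hold the item.
2. Put the undesirable-effect question to women who give birth before their 38–41 week visit through another contact, such as a telephone call.
3. State when the safety window ends.
4. Report these items as descriptive counts by arm, with no causal claim. Respect the withdrawal choices under Enrolment to the trial, so that routine data are taken after withdrawal only from women who agreed to it.

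The cost is a few fields in a look-up already planned for each of 40 women, an occasional call, and a line in the information leaflet. The downside is that events unrelated to the oil will be listed, in numbers too small to compare the arms.

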### Criteria for proceeding to the main trial

The decision to proceed to the main trial will be made by the Trial Steering Committee based on the following criteria:≥ 40% of eligible women can be recruited;≥ 70% of women adhere to the intervention and control guidelines;<  20% of women lost to follow-up.

### Data management

All data will be recorded carefully on the appropriate CRFs, which will be stored in a locked cabinet in the researcher’s work office. Quality of CRF completion will be monitored on an ongoing basis by the researcher. Only the researcher and a research assistant will have access to the paper data, while the researcher, her supervisor, a research assistant and a statistician will have access to the electronic data, which will be anonymised based on individual participant trial numbers and stored in a password-protected file on a password-protected, encrypted laptop. All data will be kept secure by the researcher for a period of five years and then shredded.

### Statistical analysis

Data will be entered into a secure database using the Statistical Packages for the Social Sciences (SPSS) version 21 [39] as collected. Data will be coded and cleaned. As this is a feasibility study, formal hypothesis testing will not be performed. Suitable descriptive statistics and graphical summaries will be used to summarise participant characteristics. Means and standard deviations will be used for continuous variables; counts and percentages will be used for categorical variables with accompanying 95% CI estimates.

In addition, numbers and percentages of women recruited, eligible, randomised, enrolled and who completed the trial will be outlined in a CONSORT flow chart.

### Intervention fidelity

Complete intervention adherence will be defined as the woman applying the allocated oil daily over approximately 26 weeks. Anything less than this will be considered incomplete adherence, with < 10 applications in total over the approximately 26 weeks being regarded as non-adherence.

